## **5 PARTICIPANTS**

### **5.1. Sampling and participant recruitment**

Stratified sampling will be used in this clinical investigation, with eight strata representing the different neurological diseases, as well as patients post stroke in the subacute and chronic phases who are severely and mild to moderately affected, respectively. This strategy will be chosen based on the primarily quantitative nature of this study.

All patients with a first-ever ischemic or hemorrhagic stroke, multiple sclerosis (MS), Parkinson's Disease (PD), a spastic para- or tetraplegia caused by any type of spinal cord lesion, mild to medium grade hereditary ataxia, acute or chronic inflammatory demyelinating polyneuropathy (e.g., GBS, CIDP) or a motoneuron disease (e.g., ALS) treated at the Reha Zentrum Münster during the recruitment period will be checked by the medical staff with regard to their suitability for participation in the clinical investigation. All patients who meet the inclusion criteria of this study and do not meet any of the exclusion criteria will be informed verbally and in writing about the study by the PI or investigator. After determining the general eligibility (inclusion criteria) and the consent of the patient i.e., their interest in participating in the study, a screening will be carried out. Using predefined criteria for intact cognitive functioning, with a cut-off score  $\geq 24/30$  points on the Mini Mental State Examination (MMSE) (Folstein et al., 1975), patients with moderate to severe cognitive impairment will be excluded. Furthermore, patients without walking impairment as defined by a neurological exam and an FAC score of 5 will be excluded. In the absence of these exclusion criteria, the study inclusion described below will take place.

After having provided the patient with the patient information sheet, an appropriate period of reflection for the patient, the opportunity for queries and answers and the patient's consent to participate, the informed consent form will then be dated and signed by both the patient and the doctor. The investigator will note the participation on a specific patient identification list. It will be used to later identify the patient and contain the identification number (ID), the full name of the patient, the date of birth and the date of admission to the clinical investigation. The patient identification list will remain at the trial centre after the clinical investigation has been completed.

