|                      | 
investigation. If they express their interest in participating, they will be screened by a psychologist for cognitive impairment and for walking impairment using the Functional Ambulation Categories in addition to a neurological exam. If patients pass the screening (if Mini Mental State Examination <math>\geq 24/30</math> points, walking impairment, FAC 0-4/5 points)), written informed consent will be obtained from them, followed by a Baseline examination. Then, the clinical investigation intervention will be conducted for 4 weeks, and a semi-structured observation of the intervention at weeks 1 and 4. After the post-intervention examination, the clinical investigation will be terminated.
                                                                                                                                                                                                                                                                                                                                                                                                                                                                                                                                                                                                                                                                                                                                                                                                                                                                                                                                                                                                               |

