In practice, this comparative multi case study will involve the analysis and synthesis of the similarities, differences and patterns across multiple cases, with the shared common goal of gaining knowledge about the feasibility, acceptability and preliminary effects of RAGT. Case selection will be performed using two different strategies: within disease groups, the 'Most Similar Systems Design' (MSSD) will be applied and between disease groups, the 'Most Different Systems Design' (MDSD) (Anckar, 2008; Przeworski & Teune, 1970) will be used, considering the 8 neurological disease groups with different symptom complexes involving distinct central and peripheral nervous system (CNS, PNS) sensorimotor system areas and pathways (upper and lower motor neurons including both the cerebrum and spinal cord, extra pyramidal motor system, peripheral nervous system and cerebellum). As for MSSD, it will mean to purposively choose study patients that are similar in as many background characteristics as possible, but without systematically matching cases on all the relevant control variables. As for MDSD, the strategy will be to purposively select patients that are as different as possible with respect to extraneous variables. The basic logic is that differences cannot explain similarities (Przeworski & Teune, 1970). Both a quantitative and qualitative data collection and analyses will be used to achieve these goals.

All cases will receive RAGT training using a standard protocol that will allow individualisation according to the neurological disease, functional status and walking performance of the patient, the stage of the disease, age of the patient etc. No control intervention will be used because this is the first study to compare a LEXO-based RAGT in patients with 7 different neurological disorders, one of them including patients at different stages of recovery and functional status (subacute, severe stroke and chronic, mild to moderate stroke).

Figure 4 presents a sample flow diagram of the clinical investigation including analyses.

[figure not shown]

**Figure 4:** Sample flow diagram of the clinical investigation including analyses

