## 4.6 Screening data

Screening for cognitive and walking impairment will be performed using two assessment strategies for each as presented in Table 5. The Mini Mental State Examination and a neurological exam are **performed within clinical routine** at the Reha Zentrum Münster (**highlighted green**), the Functional Ambulation Categories are performed **by the study PI or investigator as part of the clinical investigation (highlighted yellow) and does not involve any activity of the patient**.

**Table 5:** Screening

| Parameters         | Assessment                             | Patient inclusion if         | Scr |
|--------------------|----------------------------------------|------------------------------|-----|
| Cognitive function | Mini Mental State Examination (MMSE)   | ≥24/30 points                | x   |
| Walking impairment | Neurological exam                      | Walking impairment confirmed | x   |
| Walking impairment | Functional Ambulation Categories (FAC) | 0-4 points                   | x   |

Abbreviation: Scr=Screening.

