### 5.4 Inclusion criteria

Potential study participants must meet all listed inclusion criteria in order to be eligible for participating in this clinical investigation. Patients will be recruited into this study if they have been diagnosed with a first-ever ischemic or hemorrhagic stroke, clinically stable phase of multiple sclerosis (MS), Parkinson's Disease (PD), a spastic para- or tetraplegia caused by any type of spinal cord lesion, mild to medium grade hereditary ataxia, acute or chronic inflammatory demyelinating polyneuropathy (e.g., GBS, CIDP) or a motoneuron disease (e.g., ALS). All patients must be in a clinically stable phase of their disease. Diagnoses will be confirmed using current criteria such as the Guideline of the German Society of Neurology (2017) (Hennerici & Kern, 2017) for stroke, the revised McDonald criteria valid at the time of diagnosis (Polman et al., 2011; Thompson et al., 2018) with MS, the UK Brain Bank criteria (Hughes et al., 1992) with idiopathic PD, Guideline of the German Society of Neurology (DGN 2012) or current NICE Guideline (*Spinal injury: assessment and initial management. Spinal*

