*injury assessment: assessment and imaging for spinal injury. NICE Guideline NG41, 2016*), valid at the time of diagnosis, with spinal cord injury (SCI), the Ataxia Medical Guidelines 2016 or earlier versions, developed by Ataxia UK, London (de Silva et al., 2019) with hereditary ataxias, the diagnostic criteria originally developed by the National Institute of Neurological Disorders and Stroke (NINDS) ("Criteria for diagnosis of Guillain-Barré syndrome," 1978) in its revised version (Asbury & Cornblath, 1990; Hadden et al., 1998; Uncini et al., 2010) with GBS, the diagnostic criteria of the European Federation of Neurological Societies/Peripheral Nerve Society Guideline on the management of chronic inflammatory demyelinating polyradiculoneuropathy- First Revision ("European Federation of Neurological Societies/Peripheral Nerve Society Guideline on management of chronic inflammatory demyelinating polyradiculoneuropathy: report of a joint task force of the European Federation of Neurological Societies and the Peripheral Nerve Society--First Revision," 2010) or earlier versions with chronic inflammatory demyelinating polyneuropathy (CIDP) and the diagnostic criteria for ALS from the World Federation of Neurology as the El Escorial Criteria (Brooks, 1994), in their revised version as the Airlie House criteria (or El Escorial revised) (Brooks et al., 2000) or Awaji criteria (de Carvalho et al., 2008), or the recently developed Gold Coast criteria (Johnsen, 2020). There are no formal criteria for progressive muscular atrophy (PMA) and primary lateral sclerosis (PLS).

Patients with subacute, severe stroke who are non-ambulatory are eligible if they can be verticalised for at least 1 hour twice a day (which is a requirement for inpatient rehabilitation at the Reha Zentrum Münster). Patients with motor neuron disease in the early, active stage of the disease will be included and patients with mild to moderate hereditary ataxia. Patients will only be included if they are able to participate in this clinical investigation over its complete duration, which will be evaluated by the study PI. Further inclusion criteria will be impairment in walking according to the neurological exam assessed by a neurologist and Functional Ambulation Categories (FAC) of 0-4, intact cognitive function as defined by a score of  $\geq 24/30$  points on the Mini Mental State Examination (MMSE) (Folstein et al., 1975).

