## 8.2. Planned statistical analysis

IBM SPSS Software, release 27.0 (IBM Corporation, Armonk, NY, USA) and GraphPad Prism 9, San Diego, California, will be used for the data analyses. Statistical significance will be defined as a two-tailed p-value  $<0.05$ . The percentage of missing data will be recorded. Using Little's test of missing completely at random (MCAR) (Little, 1988) the data will be checked, signified by a p-value  $>0.05$ .

Descriptive statistics will be used for the baseline demographic variables, primary and secondary endpoints. Continuous data will be checked for normal distribution using the Shapiro Wilk Test, Q-Q plots and histograms. Raw count (absolute and relative frequencies, N (%)) will be presented for count data (N females and males, N falls, most affected body part, and N adverse events if any, adherence (N of training sessions), recruitment, retention and adherence rates) and nominal data (gender)). Medians (range; 25th and 75th percentiles) will be reported for ordinal data (MMSE, NIHSS, EDSS, UPDRS, H&Y, ASIA Scale, SARA, MAS, ONLS, ALSFRS-R, FAC, TCT, FES-I, EQ-5D-5L, BDI-II, FSS, GAS, Smiley Likert Scale), mean (standard deviation (SD)) will be reported for continuous data (age, years of education, disease duration, 10MWT, FGA, 6MWT, TUG, FSST and MFRT).

With respect to the primary endpoint of feasibility, the recruitment rate (%) will be estimated by dividing the number of consenting patients by the N of eligible patients, multiplied by 100. The retention rate determined by dividing the N of patients who completed the study by the N of the total sample, times 100. Adherence rates will be calculated by dividing the N of RAGT sessions (16x) performed by the patients, divided by the N of the scheduled RAGT training sessions over the 4 week study period, times 100 (Osterberg & Blaschke, 2005). The eligibility, recruitment and adherence rates will be calculated with their 95% CI according to the Wilson 'score' method cited by Newcombe (Newcombe, 1998); when the proportion is close to 0 or 1, a Poisson approximation as described by Brown and colleagues will be used (Brown et al., 2001). Furthermore, the number of (serious) adverse events and side effects will be reported.

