## **12.3 Patient information and consent form**

Before the clinical investigation begins, informed consent will be obtained from the patients by the investigator after they have been fully informed verbally and in writing in a way they understand about the nature, significance, and scope of the clinical investigation. The content of this information will be documented on the informed consent form. The patient will be informed if new information about the investigated intervention arises during the clinical investigation.

The patient's informed consent to participation in the clinical trial will be signed and dated by the patient and the doctor. The patient will receive a signed copy of the patient information/informed consent form. The doctor will file the second copy in the Investigator Site File. It is explicitly stated that no examinations or interventions in connection with the clinical investigation can be performed until a legally valid informed consent form has been obtained from the patient.

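### The recruitment rate divides by an 'eligible' count that the protocol uses in two incompatible ways, and the FAC is rated before written consent although section 12.3 forbids this

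*Protocol*

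**What the plan says.** The recruitment rate is part of the primary feasibility endpoint. Protocol section 8.2 obtains it by "dividing the number of consenting patients by the N of eligible patients" and gives it a 95% Wilson interval. It does not say at which step a patient is counted as eligible.

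Section 5.4 says that participants "must meet all listed inclusion criteria in order to be eligible", and the list includes "Functional Ambulation Categories (FAC) of 0-4, intact cognitive function as defined by a score of" at least 24 of 30 on the MMSE.

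On the order of events, section 5.1 says that after general eligibility and the patient's agreement, explained as "their interest in participating in the study, a screening will be carried out". The synopsis agrees: "If they express their interest in participating, they will be screened by a psychologist for cognitive impairment and for walking impairment". It then takes written consent from those who pass.

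Section 4.6 (Table 5) describes the MMSE and the neurological exam as clinical routine. The FAC is rated "by the study PI or investigator as part of the clinical investigation". Table 7 carries the screening FAC over as the baseline of endpoint 1.2.

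Section 12.3 sets this rule: "no examinations or interventions in connection with the clinical investigation can be performed until a legally valid informed consent form has been obtained".

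**The concern.** A recruitment rate in a feasibility study should tell the planners of the later randomised trial what share of suitable patients will agree to take part. It can do so only if patients who say no are counted. Here two criteria that define eligibility are tested only in patients who have already said that they are interested. Whether an early decliner counts as eligible then depends on which use of the word is applied.

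The same order raises a conduct question. A rating that the protocol itself calls part of the investigation, and whose value becomes outcome data, is made before the signature that section 12.3 requires.

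**Working it through.** The protocol states no recruitment percentage, interest rate or screen-failure rate, so there is no figure to reproduce. The only related number is the total sample: 4 strata of 5 plus 4 strata of 2 = 28 (section 5.3).

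**Two uses of eligible**

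- *After screening.* Section 5.4 requires all inclusion criteria, including FAC 0-4 and the MMSE cut-off. The FAC is rated only after interest (5.1, synopsis), so a patient who declines when informed is never shown to be eligible.
- *Before interest.* Section 5.1 informs patients who already meet the inclusion and no exclusion criteria. Section 4.5 speaks of eligible patients who then pass the cognitive screening. Table 8 puts screening after the eligibility check. On this use, decliners are in the denominator.

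**Effect on the rate**

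Of N informed patients, let i be the share interested, p the share of those passing MMSE and FAC, and s the share of those who sign. Passing is taken as independent of interest.

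- After-screening denominator: N·i·p·s / (N·i·p) = s
- Before-interest denominator: N·i·p·s / N = i·p·s
- Acceptance among fully eligible patients: i·s

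The first does not contain i. The second does, but screening failures also lower it. With assumed ranges i = 0.3-0.9, p = 0.7-1.0 and s = 0.9-1.0:

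| Quantity | Lowest | Highest |
|---|---|---|
| After-screening rate, s | 90% | 100% |
| Before-interest rate, i·p·s | 0.3 × 0.7 × 0.9 = 18.9% | 0.9 × 1 × 1 = 90% |
| Acceptance, i·s | 0.3 × 0.9 = 27% | 0.9 × 1 = 90% |

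For 28 consenting patients with i = 0.5 and p = s = 1, the number informed is 28/0.5 = 56:

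- after screening: 28/28 = 100% (Wilson 95% CI 87.9 to 100.0)
- before interest: 28/56 = 50.0% (37.3 to 62.7)

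The intervals do not overlap. Section 8.2 would switch to a Poisson approximation near 100%; Wilson is shown for both so that they can be compared. With p = 0.7 instead, 28/(0.5 × 0.7) = 80 are informed and the second rate is 28/80 = 35%.

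**Full strata.** Section 5.1 has all suitable patients treated during the recruitment period informed, while section 5.3 caps strata at 5 or 2. Nothing says whether an eligible patient whose stratum is full counts in the denominator.

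**FAC and consent.** Side by side: the FAC belongs to the investigation (4.6); it precedes written consent (synopsis); no examination connected with the investigation may precede written consent (12.3). All three cannot hold. Table 8 places screening after the patient's consent, but section 5.1 uses that word at this point for interest, so Table 8 does not resolve the conflict. Goal definition also has two timings: the screening column in Table 7, and day 0-1 after inclusion in Table 8.

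**The case against.** The strongest reply is that most of the procedural wording places eligibility before interest. Read that way, decliners are counted, and the statistical analysis plan, which is not shown, may fix the counting step. Even on the after-screening use, patients who withdraw during the reflection period still lower the rate. Success on recruitment is judged at 3 patients per month, and a screening log is kept. This stands against one inference that a reader might draw, namely that the rate must approach 100% whatever the refusal rate. The documents do not support that. It follows only from the section 5.4 use, and only for refusals at the interest stage.

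The reply does not remove the point. The protocol itself defines eligibility one way and uses it another way. An analysis plan cannot recover FAC ratings never made in decliners, nor can it change the order of rating and signature.

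On consent, a reader might also count the MMSE, the neurological exam and the pregnancy test as breaches of section 12.3. The first two are clinical routine under section 4.6, and the pregnancy test is required only before enrolment, with no stated order relative to consent. The FAC involves no activity by the patient, so the conflict is small, but section 12.3 makes no exception for that.

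A reader might finally want the case selection of section 4.1, which is to "purposively choose study patients that are similar in as many background characteristics as possible", moved into the analysis. That is a design preference. The documents do not make it an error.

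**Conclusion.** Wrong as written, on two counts.

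First, the recruitment rate has no single denominator. The contradiction comes from the text alone. Its size depends on inputs that the protocol does not give: at an assumed 50% interest, with all passing and signing, the same 28 patients can be reported as 100% or 50%. The gap narrows as interest rises: at 90% interest with p = s = 1 it is 100% against 90%. The treatment of eligible patients in full strata is also open. The percentage does not decide whether feasibility is met, but it is a reported component of the primary endpoint and is meant to inform the randomised trial.

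Second, the FAC before written consent contradicts section 12.3. This needs no assumption. The documents do not support going further and calling the baseline FAC unusable: the value is carried over only for patients who pass screening, and those enrolled then sign.

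**What to change.** 1. In section 8.2 and the synopsis, define the recruitment rate as patients who sign consent divided by all patients found eligible on chart check, including the routine MMSE and neurological exam, and informed while their stratum was open. Decliners stay in the denominator.
2. From the screening log, report the numbers informed, interested, screened, passed and consented separately.
3. Align section 5.1, the synopsis and Table 8 with section 12.3 so that written consent precedes the FAC. Reserve the word consent for the signature. Report patients who fail screening after consent separately.
4. Reconcile the timing of goal definition between Table 7 and Table 8.

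The cost is amendment wording and use of a log that section 10.2 already provides for. The reported recruitment rate will probably be lower, and a few consented patients will turn out to be screen failures.

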### **5.2 Recording adherence to the intervention**

For the intervention phase i.e., from the time of baseline testing until post-intervention testing (four weeks), a structured log will be completed by the treating physiotherapist for recording the actual performance of the planned RAGT intervention sessions or their non-performance, together with reasons.

### 5.3 Sample size

This clinical investigation will be a prospective comparative multiple case study. A comparative multiple case study design with mainly quantitative data but also qualitative data analyses and a cross-case analysis will be used. Mixing methods is a form of triangulation in research seen as mitigating the weaknesses found in single methods (Heale & Forbes, 2013). Triangulation in research is the use of more than one approach to researching a question. The objective is to increase confidence in the findings through the confirmation of a proposition using two or more independent measures (Noble & Heale, 2019). The combination of findings from two or more rigorous approaches provides a more comprehensive picture of the results than either approach could do alone (Noble & Heale, 2019). A multiple case-oriented research strategy will be adopted to acquire knowledge about the outcomes from RAGT within the 8 different patient (disease) groups, learn about similarities and differences between individual cases and neurological disorders within study intervention periods and emerging patterns (Ababacar et al., 2020; Nordbeck, 2013).

The primary outcome of this study will be the feasibility of the methods and of a larger randomised controlled trial. Based on the study design (Yin, 2014) and primary outcome, no formal sample size calculation has been carried out. Based on the different prevalence rates of the diseases investigated in this clinical investigation, 5 patients with severe stroke in the subacute phase will be included in this study, 5 patients with mild to moderate stroke in the chronic stage, 5 patients with MS, 5 patients with PD, 2 patients with spastic para- or tetraplegia caused by any type of spinal cord lesion, 2 patients with mild to medium grade hereditary ataxia, 2 patients with acute or chronic inflammatory demyelinating polyneuropathy (e.g., GBS, CIDP) and 2 patients with motoneuron disease (e.g., ALS), resulting in a total sample size of 28. Based on the study design, methods and objectives, no further patients will be included to account for attrition, which is expected at 10%.

